## Abstract

**Background::**

Fibromyalgia (FM) is a chronic pain syndrome characterized by widespread musculoskeletal pain and multiple symptoms. It is a common clinical condition whose etiology is unclear. Currently, there is no gold standard treatment for FM. Management of this condition is therefore aimed at reducing symptoms and maintaining the individual's ability to function optimally. Based on the principal symptoms and characteristics of individuals with FM, we hypothesized that the implementation of a multicomponent treatment (with physical exercise, cognitive behavioral therapy adding to a graded motor imagery program, and therapeutic neuroscience education) would be more effective than conventional treatment in women with FM. This paper describes the rationale and methods of study intended to test the effectiveness of multicomponent treatment versus conventional treatment in patients with FM.

**Method/Design::**

Fifty-six female individuals between 18 and 65 years of age, who were referred to the physical therapy department of the Rehabilitar Center in Chile, will be randomized into two treatment arms. The intervention group will receive a multicomponent treatment program for duration of 12 weeks. The control group will receive a conventional treatment for this condition for 12 weeks. The primary outcome measure will be the pain intensity score, measured by the numeric pain rating scale (NPRS), and the secondary outcomes will be the FM Impact Questionnaire (FIQ), and affective components of pain, such as catastrophizing using the Pain Catastrophizing Scale (PCS), fear of movement using the Tampa Scale Kinesiophobia (TSK), and sleep quality as measured by the Pittsburgh Sleep Quality Index (PSQI).

**Discussion::**

This paper reports the design of a randomized clinical trial aimed at assessing the effectiveness of the multicomponent treatment versus conventional treatment in women with FM.

**Trial registration::**

Brazilian registry of clinical trials UTN number U1111-1232-0862. Registered 22 April 2019.

## Introduction

1

Fibromyalgia (FM) is a chronic pain syndrome characterized by widespread musculoskeletal pain and multiple symptoms, including fatigue, sleep disturbance, cognitive dysfunction, and psychological distress.^[1,2]^ It is one of the most common chronic pain conditions, with a worldwide prevalence of 2%, and is found in 1% to 4.9% of women and in 0% to 2.9% of men.^[3,4]^

The etiology of FM is unclear; however, central mechanisms are strongly implicated, including evidence of abnormalities in structure, function, and molecular chemistry of the central nervous system.^[5–7]^ A common finding in chronic pain syndromes is central sensitization, which is defined as an increased responsiveness of the central nervous system to a variety of stimuli (e.g., pressure, temperature, light, and medication).^[8]^ This central hyperexcitability causes hyperalgesia, allodynia, and referred pain across multiple spinal segments, and has been show in patients with FM.^[9,10]^

Management of FM is aimed at reducing symptoms and maintaining the individual's ability to function optimally,^[11,12]^ but currently there is no gold standard treatment for FM. Some guidelines and systematic reviews showed that the efficacy of pharmacological treatment was questionable and had a modest effect on patients with FM.^[13–16]^ Moreover, some evidence indicates that treatments which include multiple non-pharmacological components have beneficial effects on key FM symptoms, although effects are limited and often do not persist over time.^[17,18]^ Factors that could affect this poor response to treatment include fear of movement and catastrophization in individuals with FM.^[19–21]^

Multicomponent treatment, involving a combination of aerobic exercise and cognitive behavioral therapy, has shown some evidence as a moderate treatment of FM.^[22,23]^ However, the multifactorial component of FM and its wide variety of symptoms could interfere with treatment success,^[20,24]^ and affective components, such as poor pain coping, catastrophization and kinesiophobia, have been associated with poorer treatment outcomes in FM.^[21,25]^ Ignoring these individual differences may compromise the evaluation of treatment outcomes.

Graded Motor Imagery (GMI) and Therapy Neuroscience Education (TNE) are therapeutic tools successfully used in a number of conditions.^[26–29]^ The aim of GMI and TNE is to facilitate sensory and motor cortex reorganization, decrease pain, and improve function in patients with chronic musculoskeletal pain.^[30,31]^ Additionally, TNE is aimed at teaching patients about the neurobiology, neurophysiology, processing, and representation of pain in the central nervous system.^[32]^ Both treatments can be individually adapted and include neurophysiological adaptations, which could have benefits in the treatment of the individual needs of patients with FM.

Unfortunately, no evidence has been found regarding the combined use of these treatments in a multicomponent therapy for patients with FM. This paper reports the rationale and methods of a single-blinded, randomized controlled trial aimed at assessing the effectiveness of a multicomponent treatment involving physical exercise, cognitive behavioral therapy adding to a GMI program, and a TNE program, on pain relief, affective components, and functional improvement, as compared to conventional treatment in women FM patients over 18 years of age.

## Method

2

### Study design/setting

2.1

This protocol was reported based on Standard Protocol Items: Recommendations for Interventional Trials (SPIRIT) guidelines.^[33]^ This study will be a single-blinded, randomized controlled trial with two parallel groups. It will be conducted at the Physical Therapy Department of the Rehabilitar Center in Chile. The participants will be informed about the research, the procedures, the risk, and the benefits by [name] (author of this protocol). After their agreement, participants must sign the informed consent form to be involved in the study, following the schedule as described in Figure 1.

**Figure 1 F1:**
[figure not shown]
Standard protocol items: recommendations for Interventional Trials (SPIRIT) figure.

### Participants

2.2

A total of 56 adult females with FM, diagnosed by a rheumatologist based on the clinical history and the American College of Rheumatology criteria, will be included in this study.^[34]^ The American College of Rheumatology criteria are: general muscle pain, fatigue sensation, unrestful sleep, and cognitive dysfunction. These clinical signs have shown sensitivity and specificity values above 90% for the diagnosis of FM.^[34,35]^

### Inclusion criteria

2.3

To participate in the study individuals must fulfil the following inclusion criteria:

1.women with FM over 18 years old attending the Physical Therapy Department of the Rehabilitar Center, with a clinical diagnosis based on the clinical criteria of the American College of Rheumatology,2.a pain intensity above 4 out of 10 on the Numeric Pain Rating Scale (NPRS),3.the ability to follow simple instructions, and4.willing to accept and sign the informed consent.

### Exclusion criteria

2.4

Conversely, patients with the following conditions will be excluded:

1.pregnancy and/or lactation,2.chronic cancer pain,3.metabolic disorder and/or uncontrolled comorbidities,4.some degree of cognitive impairment, scoring < 26 points on the Mini-Mental State Test (MMST).

### Interventions

2.5

This study will be a single-blinded, randomized controlled trial with two parallel groups. The intervention group will receive a multicomponent treatment based on physical exercise, cognitive behavioral therapy adding to a GMI program, and a TNE program. In the initial stage, TNE will be used to decrease pain, fear avoidance, and disability.^[32,36]^ The TNE component aims to educate individuals on how pain is processed by the nervous system,^[37]^ using images, examples, metaphors, and drawings, as needed, during twice-weekly sessions for 2 weeks, each session being an average of 60 min duration. To ensure a standardized TNE program, a systematic checklist will be developed. Patients will also receive a booklet summarizing the educational content of the session, including images, examples, and metaphors about chronic pain and about their clinical condition. Patients will be asked to read the TNE booklet at least once a day.

The GMI program will include three steps: laterality training, imagined movements, and mirror therapy. Laterality training is the first step in the GMI program, designed to improve the accuracy of the patient's cortical representation of his/her body. The patient trains by looking at left and right images of body parts in different positions using the Recognize application, created by the Neuro Orthopaedic Institute (NOI). The application records both accuracy and response time and allows the user to set the difficulty of the images by modifying context and background. Training is carried out for 1 h per day, in short sessions using 20 images. Laterality training will be progressed by increasing the number and difficulty of the images involved.

The second step of the GMI program will be imagined movements, aimed at preparing the patient to move. The exact instructions that will be given are: "imagine that you are involved with the body in the illustrated positions without really moving in. Imagine each position twice, and repeat the whole process three times a day.” Imagined movements will be involved with anterior flexion, abduction and rotations, depending on the body segment being treated. The patients will be provided with photographs or diagrams of the positions which are to be imagined. Imagined body movements are reported to activate the cortex in a similar way to executed movements.^[38]^

The last stage of the GMI program will be mirror therapy. The patients will be instructed to look at the mirror image of the unaffected body segment and to move that body segment in different ways. This creates the illusion that the body is moving pain–free and provides strong, positive, sensory cortical feedback that movement does not have to be painful, and may disprove cognitions of the mind, thus allowing the patient to believe pain-free movement is possible.^[39]^ Individuals are instructed to assign a body segment with the greatest symptomatology in the last 7 days.^[40]^ Patients will perform mirror therapy in two weekly sessions for 2 weeks.

An exercise program will be prescribed based on the individual's maximum heart rate, determined by polar M600^[41]^ starting just below their capacity and gradually increasing in duration and intensity. Physical activity sessions will include aerobic and stretching exercises based on the recommendations of the American Society of Sports Medicine,^[42]^ including 10 min warm-up, 40 min of effective aerobic exercise involving step, walking, and functional exercises with physiotherapy tools, and 10 min cool down including stretching exercises and a soft walk for 5 min, with deep breathing and global movements. The session will be performed twice a week for 4 weeks.

The cognitive behavioral therapy program prescribed will include group sessions of education about FM and pain perception theory, cognitive restructuring skills training, emotional stress management, and family problem resolution. All sessions will be carried out weekly for 1 h over an 8-week period.^[43]^

In the control group, all patients will receive pharmacotherapy and a conventional treatment program based on standard education by the physician. In the first session, the patient will be evaluated on comorbidities and clinical condition, and will receive health education on pain using standard images and graphic examples. Secondly, each patient will be prescribed duloxetine 60 mg, pregabalin 300 mg, milnacipran 100 mg and vitamin D 200 mg. Each dose will be evaluated and modified in relation to the requirements of each patient and taking into account the possible adverse effects.^[44,45]^ In the final session, each patient will be prescribed cyclobenzaprine 5 mg and adverse effects and the need for new medication will again be evaluated again. This will be performed once a week for 12 weeks. To monitor adherence to treatment, patients will be contacted by phone at the end of each week of treatment.

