### Sample size calculation

2.10

Sample size for this trial is based on an expected mean difference between groups of 2 points of the NPRS, which is the minimum clinically important difference.^[63]^ The mean assumed for the calculation was 5.95, with a standard deviation (SD) of 2.06 points, based on results of other randomized clinical trials.^[64]^ To detect this difference between the control and intervention groups, with a value of α = 0.05 (probability of committing a type I error) and a statistical power of 90%, a minimum of 22 patients per group is needed. This minimal sample size estimate has been increased by 20%, taking into consideration the potential dropouts, giving a total of 28 patients for each group. Sample Size was performed using the Stata SE software, version 15 (StataCorp, College Station, TX).

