### Statistical analysis

2.14

The continuous variables will be presented as mean and standard deviation, and the categorical variables as number and percentage. To determine whether parametrical statistical tests are appropriate for the analysis of the data, the fitting to normal distribution will be evaluated using both statistical (Shapiro–Wilk test) and graphical (normal probability plot) methods. To examine baseline differences, a Student t-test will be used with interval variables, and Chi-squared with nominal ones. Analysis of covariance (ANCOVA) will be used for differences between groups at twelve weeks in primary and secondary outcomes using continuous scales, with adjustment for baseline levels of outcomes, using group differences in the mean change from baseline to twelve weeks as dependent variable. Finally, in the event of possible losses or dropouts, a statistical analysis will be carried out by protocol and intention to treat.

Data will be processed independently by two researchers, and inconsistencies will be detected using the VALIDATE command of the Epi Info (CDC) software. After checking for true outliers and extreme values, data will be winsorized using results below the 1st percentile and above the 99th percentile of the distribution of variables. Prior to analyzing the data, we will check for missing data and consider applying imputation methods using chained equations.

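### CBT is given in groups in the intervention arm only, but the sample size and the ANCOVA assume independent patients; any positive within-group correlation would make the interval too narrow and leave the 90% power without allowance for it

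*Protocol article*

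**What the plan says.** Four parts of the protocol article bear on this.

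- **Delivery, intervention arm (2.5 Interventions).** "The intervention group will receive a multicomponent treatment based on physical exercise, cognitive behavioral therapy adding to a GMI program, and a TNE program". On CBT: "The cognitive behavioral therapy program prescribed will include group sessions of education about FM and pain perception theory". The sessions are weekly, one hour each, over eight weeks. Group size and number of groups are not stated.
- **Delivery, control arm (2.5 Interventions).** "In the control group, all patients will receive pharmacotherapy and a conventional treatment program based on standard education by the physician". Care is described patient by patient and no group session is mentioned. Individual delivery is the natural reading, although the article does not say so in terms.
- **Sample size (2.10).** "Sample size for this trial is based on an expected mean difference between groups of 2 points of the NPRS". "The mean assumed for the calculation was 5.95, with a standard deviation (SD) of 2.06 points". With α = 0.05 and 90% power the article concludes that "a minimum of 22 patients per group is needed", raised to 28 for 20% dropout. No ICC, group size or design effect enters.
- **Analysis (2.14).** "Analysis of covariance (ANCOVA) will be used for differences between groups at twelve weeks in primary and secondary outcomes using continuous scales", adjusted for the baseline value. There is no term or variance correction for CBT group.

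**The concern.** Patients who attend the same CBT group share sessions and fellow patients for eight weeks, and the primary outcome is self-rated pain in unblinded patients. Their week-12 scores may therefore resemble one another more than those of patients from different groups. Control patients have no such grouping. This is a partially nested design: clustered in one arm, unclustered in the other.

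An ANCOVA that assumes independence counts the intervention arm's information as if every patient contributed separately. With a positive within-group correlation, the standard error of the treatment difference is too small, the nominal 95% interval covers less than 95%, and the test rejects a true null hypothesis more than 5% of the time. The power calculation uses the same assumption. If CBT group membership is not recorded, the point may be impossible to examine later.

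**Working it through.** **1. Reproduce the stated figure.** Inputs from section 2.10: difference 2, SD 2.06, α = 0.05 (taken as two-sided), power 90%.

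n per arm = 2 × [2.06 × (1.960 + 1.282) / 2]² = 22.29, against the stated 22. The difference is rounding and is not pursued. At 22 per arm, SE = 2.06 × √(2/22) = 0.621; power is 89.6% by normal approximation and 88.2% by noncentral t with 42 df. Then 22 / 0.80 = 27.5, rounded up to 28. The plan's figure is what full independence gives, with no design effect in it.

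**2. Allow for clustering in one arm.** Assumptions, not in the document: CBT groups of m = 7 (28 patients in four groups) or m = 14 (two groups), and ICC 0.02, 0.05 or 0.10.

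Variance of the difference = SD² × {[1 + (m − 1) × ICC] / n + 1 / n}. Relative to independence with equal arms, this is an inflation of 1 + (m − 1) × ICC / 2.

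- m = 7: 1.06, 1.15, 1.30. The true SE is larger by a factor √inflation: 3%, 7%, 14%.
- m = 14: 1.13, 1.325, 1.65. The true SE is larger by 6%, 15%, 28%.

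**3. Type I error of the independent-data test.** The normal approximation is 2 × [1 − Φ(1.96 / √inflation)]. Simulation used 28 per arm and 40,000 trials per setting.

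| Groups | Method | ICC 0.02 | ICC 0.05 | ICC 0.10 |
|---|---|---|---|---|
| 4 of 7 | simulation | 5.8% | 6.4% | 8.5% |
| 4 of 7 | formula | 5.7% | 6.8% | 8.6% |
| 2 of 14 | simulation | 6.7% | 8.9% | 13.0% |
| 2 of 14 | formula | 6.5% | 8.9% | 12.7% |

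The two methods agree within half a percentage point.

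**4. Power for 2 points at 22 per arm, m = 7, no credit for baseline adjustment.** The SE is 0.621 × √inflation = 0.639, 0.666, 0.708.

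Patient-level df is 42. Cluster-based df uses the Satterthwaite form, (vI + vC)² / [vI² / (k − 1) + vC² / 21], with k = 22 / 7 = 3.14 groups. At ICC 0.05, vI = 4.2436 × 1.30 / 22 = 0.2508 and vC = 4.2436 / 22 = 0.1929, so df = 0.1968 / (0.02934 + 0.00177) = 6.3.

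| ICC | SE | Power, 42 df | Cluster-based df | Power, cluster-based df |
|---|---|---|---|---|
| 0 | 0.621 | 88% | 7.8 | 80% |
| 0.02 | 0.639 | 86% | 7.1 | 77% |
| 0.05 | 0.666 | 83% | 6.3 | 72% |
| 0.10 | 0.708 | 79% | 5.4 | 64% |

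The first row matters: with about three groups, the cluster-based df alone costs some 8 points even when the correlation is zero.

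**5. Offsets.** Section 2.10 uses the raw SD, while section 2.14 adjusts for baseline. With an assumed baseline correlation of 0.5, the residual SD is 2.06 × √0.75 = 1.784. Power at 22 per arm, m = 7, 42 df, is then 94%, 92% and 89%; with a correlation of 0.3 it is 89%, 87% and 82%. If all 28 per arm complete, with no baseline credit, power with patient-level df is 91% at ICC 0.05 and 88% at 0.10; with cluster-based df it is 85% and 79%.

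**The case against.** **The size rests on assumptions.** Group size, number of groups and ICC are not in the article, and an ICC as high as 0.10 has no support there. A reader might infer that the interval certainly is too narrow and the trial certainly is underpowered. The article does not support that: both follow only if the correlation is positive, and at ICC 0.02 with groups of 7 the SE rises by 3% and power goes from 88% to 86%.

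**Shared exposure may be limited.** A reader might also infer a shared therapist and fixed groups. Neither is stated, and recruitment from April to December 2019 means staggered entry, so groups could be open or rolling. Group format is stated for CBT alone. Exercise is set from individual heart rate, and the imagery work uses an application and pictures. This argues for a low ICC, not for zero.

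**The power loss may be offset.** It may, as step 5 of the working shows, through baseline adjustment or low dropout. Neither offset corrects the standard error or the type I error.

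**The remedy could cost more than the problem.** This stands in part. With two to four groups, the group variance is poorly estimated and small-sample df reduce power markedly, so making the nested model primary is a debatable trade.

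**A condensed article may leave this to a fuller plan.** A sensitivity analysis could be there. But the article itself fixes an independent-data ANCOVA and a 90% power figure, and those are what is questioned.

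**Conclusion.** The point holds conditionally. The article describes group CBT in one arm and fixes a sample size and an ANCOVA that both assume independence. For any positive within-CBT-group correlation, the planned interval is too narrow and the 90% power does not allow for it.

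The size cannot be settled from the article. Under the assumed range (groups of 7 or 14, ICC 0.02 to 0.10), type I error runs from just under 6% to 13%. Without baseline credit, at 22 per arm and groups of 7, power is 79% to 86% with patient-level df or 64% to 77% with cluster-based df. These two power ranges belong to different analyses: the first must not be quoted for a model that uses small-sample df. The final power shortfall could be small. The concern about the standard error remains whatever the offsets. It is worth correcting because the remedy is cheap now, but it does not show that the trial is invalid or that the primary model must be replaced.

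**What to change.** 1. Record on the case report form the CBT group number of each intervention patient, and state the planned group size and whether membership is fixed or rolling.
2. Pre-specify, at least as a sensitivity analysis of the primary outcome, the same ANCOVA with a random intercept for CBT group in the intervention arm only and small-sample degrees of freedom.
3. State in section 2.10 that the 90% power assumes no correlation within CBT groups. Give the range under stated group size and ICC assumptions, naming the degrees of freedom used and any credit taken for baseline adjustment.

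**Cost.** One variable and one model term. The interval will be wider, and with few groups the between-group variance will be imprecise, which is why a sensitivity analysis is a sufficient minimum.

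Restating power needs no extra patients; keeping 90% without baseline credit would. By normal approximation, n per arm = (22.29 / 2) × [2 + (m − 1) × ICC]. For m = 7 this gives 24, 26 and 29 at ICC 0.02, 0.05 and 0.10, or 30, 33 and 37 after dividing by 0.80, against the planned 28. Small-sample df would raise these further.

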### Recruitment

2.11

Recruitment of the participants begun in April 2019 and is expected to finish in December 2019. Information on the study goals and procedures will be verbally provided. The participants will also be invited to raise questions or doubts on any aspect of the study. Data confidentiality guarantees will be provided to participants by the principal investigator. Written consent will be obtained from all participants before registration, and participants may withdraw from the trial at any point in time without penalties. The written consent form includes information regarding the background and purpose of the study, therapeutic interventions, outcomes, and the expected benefits and drawbacks.

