### Harms

2.15

Patients from both groups will have a logbook available during each session, in order to collect, assess, report, and manage the potential adverse effects of the interventions that will be performed in the study. According to the informed consent, patients who show an increase in symptoms after 48 h of the session will be immediately evaluated by an rheumatologist.

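### The control-arm vitamin D dose is printed as 200 mg, about 8,000,000 IU: almost certainly a unit misprint, to be checked and corrected

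*Protocol article*

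**What the plan says.** The control regimen is described in section 2.5 of the protocol article (Interventions). After an opening session of assessment and education, "each patient will be prescribed duloxetine 60 mg, pregabalin 300 mg, milnacipran 100 mg and vitamin D 200 mg". The sentence is running text and applies to every control patient. It gives no IU equivalent, form of vitamin D or dosing interval, and no other part of the article repeats or corrects the amount.

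The article also describes supervision around this prescription:

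- Section 2.5, before prescribing: "In the first session, the patient will be evaluated on comorbidities and clinical condition".
- Section 2.5, after prescribing: "Each dose will be evaluated and modified in relation to the requirements of each patient and taking into account the possible adverse effects". Adverse effects are reviewed again at the final session.
- Section 2.5, as an adherence check: "patients will be contacted by phone at the end of each week of treatment".
- Section 2.4 (Exclusion criteria) keeps out patients with "metabolic disorder and/or uncontrolled comorbidities".
- Section 2.15 (Harms) provides a logbook for adverse effects in both groups and adds that "patients who show an increase in symptoms after 48 h of the session will be immediately evaluated", by a rheumatologist.

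On numbers and timing, section 2.10 (Sample size calculation) ends by "giving a total of 28 patients for each group", and section 2.11 states: "Recruitment of the participants begun in April 2019 and is expected to finish in December 2019".

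**The concern.** Vitamin D is usually dosed in micrograms or IU, and 200 mg is far outside any amount one would expect. Every other drug named for the control arm is given in milligrams (60, 300 and 100, and later 5 for cyclobenzaprine), so a unit carried along the list is a natural explanation.

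Two things are at stake. First, safety: on any reasonable assumption about vitamin D dosing, the printed amount would be unsafe if someone followed it literally. Second, the definition of the comparator: the vitamin D is part of what each control patient is prescribed, so it belongs to the treatment that the multicomponent programme is compared with. Anyone repeating or auditing that arm needs to know the dose. This is a point about treatment specification; it is not an error of inference.

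**Working it through.** The article does not derive the dose from anything else, so there is no calculation of its own to reproduce. The check is a unit conversion followed by a comparison with a range.

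**Inputs**

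- Printed dose: 200 mg (protocol article, section 2.5).
- Assumption 1, not in the article: 1 microgram of vitamin D = 40 IU.
- Assumption 2, not in the article: a plausible single dose lies between 400 IU (a small daily supplement) and 600,000 IU (a very large one-off dose). The range is set wide on purpose. In mass units it runs from 400 / 40 = 10 micrograms = 0.01 mg to 600,000 / 40 = 15,000 micrograms = 15 mg.
- Planned control arm: 28 patients (section 2.10).

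**Step 1. The printed dose in IU**

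200 mg × 1,000 = 200,000 micrograms; 200,000 × 40 = 8,000,000 IU.

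**Step 2. The two obvious alternative units**

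| Reading | Micrograms | IU | Printed dose is larger by |
|---|---|---|---|
| 200 mg (as printed) | 200,000 | 8,000,000 | – |
| 200 micrograms | 200 | 200 × 40 = 8,000 | 8,000,000 / 8,000 = 1,000 |
| 200 IU | 200 / 40 = 5 | 200 | 8,000,000 / 200 = 40,000 |

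The two alternatives differ from each other by 8,000 / 200 = 40.

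**Step 3. The printed dose against the assumed range**

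| Assumed single dose (IU) | 8,000,000 IU divided by it |
|---|---|
| 600,000 | 13.3 |
| 50,000 | 160 |
| 4,000 | 2,000 |
| 400 | 20,000 |

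**Step 4. Sensitivity to the assumption**

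If the upper limit is raised tenfold, to 6,000,000 IU, the printed dose still exceeds it (8,000,000 / 6,000,000 = 1.33). The conclusion does not depend on where within reason the upper limit is placed.

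**Step 5. Does anything else in the article settle the dose?**

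No. The dose-modification clause adjusts from the prescribed starting dose and does not restate it. The assessment, exclusion and harms provisions name no vitamin D amount.

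**The case against.** The strongest case on the other side has four parts.

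*The article does not contradict itself.* It gives no second dose, so the discrepancy appears only once a conversion factor and a comparison range are brought in from outside. That is true, and both are labelled above as assumptions. The factor is a plain unit conversion, however, and the range is wide enough that its exact limits do not matter.

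*The cause may not be the unit.* The number could be wrong, or 200 mg could be the mass of a preparation, or a total instead of a single dose. This stands as a caution. A misprinted unit is the likeliest cause but is not proved, which is why the correct amount and unit are left to the investigators.

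*The risk is contained and may exist only on paper.* A physician assesses each patient first, doses are modified individually, adverse effects are logged and reviewed, and worsening symptoms lead to evaluation. The article also condenses an ethics-approved protocol (section 2.16) that is not shown and may be right. All of this makes literal use unlikely. The comparison range is also not a toxicity threshold, so no specific harm is quantified. None of this corrects the printed figure, and condensing explains missing detail, not a wrong unit.

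*A check of prescribing records goes too far.* It could be made conditional on the approved protocol also reading 200 mg. That ordering is sensible: the protocol should be looked at first. With enrolment already open and at most 28 records involved, confirming what was actually prescribed remains proportionate.

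**Conclusion.** The concern holds. As printed, the control-arm vitamin D dose equals 8,000,000 IU under the assumed 40 IU per microgram. That is 13.3 times the top of a deliberately generous assumed range and 20,000 times the bottom. A misprint, most likely of the unit, is almost certain, although the article alone cannot prove it or show which amount was intended.

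The point should be fixed because it is a stated, safety-relevant dose in the defined comparator. It is limited to vitamin D. There is no evidence that anyone received the printed amount, and the endpoints, sample size and analysis are unaffected.

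**What to change.** 1. Compare the vitamin D entry with the working, ethics-approved protocol.
2. Correct the amount and unit in section 2.5 of the article. The investigators must state which amount is right; it should not be inferred from the printed number.
3. Confirm from the prescribing records of the control patients enrolled so far that the intended dose was used.

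The cost is a one-line correction and a review of at most 28 records. No extra patients, visits or analyses are needed.
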